## List of Abbreviations

|        |                                                                       |
|--------|-----------------------------------------------------------------------|
| ABLE   | Accelerating Botswana through the Last Mile to Epidemic Control       |
| BIC    | Bayesian information criterion                                        |
| BSMART | Botswana smoking abstinence and reinforcement trial                   |
| BUMMHI | Botswana University of Maryland School of Medicine Health Initiative  |
| DSMB   | Data safety and monitoring board                                      |
| EMR    | Electronic medical records                                            |
| ERIC   | Expert recommendation for implementing change                         |
| FWA    | Federal-wide assurance                                                |
| HRDC   | Health research development committee                                 |
| ICER   | Incremental cost-effectiveness ratio                                  |
| INMB   | Incremental net monitoring benefit                                    |
| IPMS   | Integrated patient management system                                  |
| IRB    | Institutional review board                                            |
| LHW    | Lay health workers                                                    |
| LMIC   | Lower middle-income countries                                         |
| MOHW   | Ministry of Health and Wellness                                       |
| NADM   | Non-AIDS-defining malignancy                                          |
| NAHPA  | National AIDS and health promotion agency                             |
| NB     | Net benefit                                                           |
| NPD    | Nurse prescriber/ dispenser                                           |
| OHRP   | Office for human research protections                                 |
| PIMS   | Patient information management system                                 |
| PLWH   | People living with human immunodeficiency virus                       |
| POSA   | Probabilistic one-way sensitivity analysis                            |
| PSAT   | Program sustainability assessment tool                                |
| RE-AIM | Reach effectiveness adoption implementation and maintenance framework |
| SAE    | Serious adverse events                                                |

|       |                                                          |
|-------|----------------------------------------------------------|
| SBIRT | Screening, brief intervention, and referral to treatment |
| SOC   | Standard of care                                         |
| SPP   | Suicide prevention plan                                  |
| SSA   | sub-Saharan Africa                                       |
| UMB   | University of Maryland Baltimore                         |

## Protocol Summary

Tobacco use is highly prevalent among people living with HIV/AIDS (PLWH), especially in southern Africa where HIV is most heavily concentrated. Among PLWH, tobacco use impacts HIV-related co-morbidities and is also the leading cause of premature mortality from non-HIV related malignancies such as lung cancer which account for 20% of the cancer burden. Integrating an evidence-based intervention, such as Screening, Brief Intervention and Referral to Treatment (SBIRT) into a HIV care system presents an important opportunity to establish and evaluate a modifiable cancer prevention strategy into a low-middle-income country (LMIC) setting where both lay health workers (LHW) and non-physician clinicians are widely used. Botswana, where the University of Maryland Baltimore (UMB) has worked since 2015, oversees a wide network of HIV care clinics for its citizens. Demographic Health Surveys from sub-Saharan Africa show that smoking prevalence among PLWH ranges between 12.5-44.3%. Yet, based on our pilot data, the system of care is highly unprepared to meet the challenge of integrating evidence-based smoking cessation treatment into routine HIV care.

The Government of Botswana wants more to be done to assist its citizens in smoking cessation. To meet this challenge, the **Botswana Smoking Abstinence Reinforcement Trial (BSMART)** proposes to use a Type 2 hybrid effectiveness-implementation study design to evaluate the effectiveness and implementation of a well-established Screening, brief intervention, and referral to treatment (SBIRT) intervention consisting of the 5“A”s, (Ask, Advise, Assess, Assist, Arrange) delivered by trained LHW case managers, followed by referral to treatment with varenicline (a medication demonstrated to be efficacious for smoking cessation among PLWH prescribed and monitored by trained nurse prescribers/dispensers, in the network of outpatient HIV care facilities in Botswana.

The study objectives guided by the RE-AIM Framework and informed by an Implementation Governance Structure are to:

- 1) Assess **Reach** and **Effectiveness** of BSMART;
- 2) Assess the **Adoption** and **Implementation** indexed by quality and consistency of intervention delivery;
- 3) Assess whether the intervention becomes **Maintained** as part of routine practices; and
- 4) Determine the preliminary cost-effectiveness of BSMART.

## Introduction

### Background

Cancer epidemiology among people living with HIV (PLWH) has shifted since the introduction of antiretroviral therapy (ART). Over the last 10 years, rates of AIDS-defining malignancies, including Kaposi sarcoma, non-Hodgkin's lymphoma, and cervical cancer have decreased, while rates of many non-AIDS-defining malignancies (NADMs) substantially increased. Lung cancer is the most common NADM among PLWH, accounting for 20% of the cancer burden. Lung cancer incidence has been consistently reported as greater in PLWH than persons living without HIV with an excess risk of 52% among PLWH compared with the general population. Lung cancer control and prevention is an area of major clinical and public health interest for PLWH.

Among PLWH, tobacco use has been consistently shown to impact HIV-related co-morbidities and has also been identified as the leading cause of premature mortality from non-HIV related cancers. Smoking continues to be a major risk factor for lung cancer in the HIV infected population. The incidence of lung cancer is almost 3-4-fold among PLWH tobacco smokers than nonsmokers and develops at a younger age in PLWH compared to the general population. Most lung cancers in HIV-infected patients occur in current or former heavy smokers. A modeling analysis looking at the risk of lung cancer death due to smoking among PLWH showed that those who continued to smoke were six to 13 times more likely to die from lung cancer than from AIDS-related causes. In our view, shared by others in the field, the single greatest health behavior change that could improve mortality is to assist smokers living with HIV/AIDS to quit smoking.

Tobacco consumption in SSA is rising as tobacco companies increasingly target this region. Evidence indicates that the highest proportion of tobacco smokers are clustered in Southern African countries – Botswana, Lesotho, and South Africa (Figure 1.). This is particularly noteworthy given that Southern Africa is also the region with the highest prevalence and incidence of HIV globally (Figure 2).

[figure not shown]

Figure 1: Prevalence of smoking in Botswana

[figure not shown]

Figure 2: Prevalence of HIV in Africa

The Parliament of Botswana had in August 2021, passed a Tobacco Control Bill, which is currently awaiting signature by the President of Botswana. This Bill, which is sponsored by the Minister of Health and Wellness aims to discourage smoking initiation, encourage quitting, and reduce tobacco consumption overall to address prevention and control of non-communicable diseases such as lung cancer. The Global Adult Tobacco Survey conducted in 2017 shows that while the majority of smokers in Botswana made an attempt to quit in the past 12 months, only 7% of smokers were able to successfully quit. The Government of Botswana wants more to be done to assist its citizens in smoking cessation.

The average years of life lost by PLWH smokers compared with HIV-positive non-smokers have been estimated as 12.3 years, which is more than twice the number of years lost by HIV infection alone. Botswana is particularly vulnerable because of its near transition from a Stage 1 tobacco smoking epidemic (prevalence of cigarette smoking <20%) to a Stage 2 (rapid increase in male smoking and prevalence beyond 20%). It is expected to face the largest growth in tobacco consumption in the world. If interventions for PLWH can be designed and implemented at scale, a significant impact on lung cancer control can be achieved.

## Rationale

The Botswanan Government has recognized that smokers, especially those who are living with HIV, need additional assistance beyond the standard smoking cessation services. The Ministry of Health and Wellness is therefore calling for implementation science that uses proven evidence-based interventions for smoking cessation that can be deployed at scale for HIV care facilities at an acceptable cost.

HIV care settings provide opportunities for early intervention with patients who smoke. The Ministry of Health and Wellness has expressed enthusiasm for leveraging the use of lay health workers in smoking cessation programs. Lay health workers are considered critical in filling the human resource constraints in Botswana, and thus the most appropriate and efficient route of delivery of counseling-based smoking cessation within the context of sustainability and scalability. In addition, there is a growing body of evidence supporting the effectiveness of the SBIRT (Screening and brief intervention, and Referral to treatment) intervention in a variety of settings. The use of SBIRT has been found to not only increase the likelihood of making a tobacco quit attempt among patients who received a brief intervention, but it has also been strongly and consistently associated with increased satisfaction with care provided. In a

review of literature examining the use of SBIRT for tobacco cessation, studies suggest that even low-intensity SBIRT may prompt quit attempts, decrease cigarette use, and facilitate quitting, if offered routinely. We have adapted the SBIRT approach by creating trainings that would allow lay health workers to deliver the 5 “A”s tailored to the unique needs of PLWH. The likelihood of a successful quit attempt is increased if counseling is provided along with pharmacologic therapy especially for individuals who smoke and are willing to quit.

We plan to use varenicline, a high-affinity partial agonist for the nicotinic acetylcholine receptor subtype, which has been shown to be more efficacious than nicotine replacement therapy or bupropion in a large pharmacotherapy smoking cessation trial. The rationale for choosing varenicline is based on many factors including availability, cost, and efficacy. Currently, smoking cessation pharmacological interventions available in Botswana are limited to nicotine replacement therapy (NRT) which can be purchased over the counter (cost: \$28/month). and varenicline which requires a prescription (cost: \$50/month). Of note, a pack of cigarettes costs about \$7 (or about \$210/month [one pack per day]) which makes smoking almost eight times as expensive as NRT. Additionally, some participants may prefer not to use NRT given past experience of side effects, lack of effect or strong preference not to use it which may limit their interest in participating in the study or following through with study procedures. Finally, the effects of NRT have been mixed; though two randomized control trials demonstrated efficacy of NRT both alone and combined with behavioral therapy, two randomized control trials showed no effect of NRT on cessation rates. Varenicline, however, consistently demonstrated efficacy in two randomized control trials among PLWH.

Supported by the Botswanan Ministry of Health and Wellness and with sustainability and scalability in mind, the Botswana Smoking Abstinence Reinforcement Trial (BSMART) will use a Type 2 hybrid effectiveness-implementation study design, informed by the RE-AIM framework to evaluate the effectiveness, implementation and preliminary cost-effectiveness of a well-established SBIRT intervention (consisting of the 5”A”s) delivered by trained LHW case managers, followed by referral to treatment with varenicline prescribed and monitored by trained clinicians in a network of outpatient HIV care. The study objectives are as follows:

1. To assess the Reach and Effectiveness of BSMART.
  - i. Reach is defined as the proportion of PLWH who agree to participate and screen in the intervention program,

- ii. Effectiveness is defined as a 7-day biochemically verified point prevalence abstinence from combustible tobacco products at 6 months using CO Check+. Our sample size (n=750 participants) has sufficient power to show at least 8% increase in a clinical effectiveness endpoint in the implementation group relative to standard of care (SOC) in the control group.
- 2. To assess the Adoption and Implementation of BSMART indexed by quality and consistency of intervention delivery.
  - i. identify how BSMART can be tailored to the network of HIV clinics in Botswana for adoption and implementation fidelity,
  - ii. foster comparison across clinical sites, and
  - iii. inform the development of activity logs to track implementation strategies.
- 3. To assess whether the intervention becomes Maintained as part of routine practices over time across HIV care facilities.
  - i. determine the extent to which the core components of BSMART and implementation strategies continue to be delivered and are maintained over time with fidelity and
  - ii. using the Program Sustainability Assessment Tool (PSAT), determine how organizational capacity and infrastructure to deliver BSMART are maintained, including partnerships, networks, and coalitions.
- 4. To determine the preliminary cost-effectiveness of BSMART - the incremental net monetary benefit at 6 months of follow-up in order to compare the value of BSMART to standard of care (SOC).

### **Hypothesis:**

The BSMART intervention (SBIRT and varenicline) will

- i. Increase the proportion of smokers able to quit smoking
- ii. Increase the number of attempts to quit smoking
- iii. Increase the length of abstinence in failed quit attempts
- iv. Decrease the number of cigarettes smoked every day
- v. Decrease the number of days of using combustible products within the past month
- vi. Decrease the number of days of using combustible products within the past three months in people exposed to the intervention as compared to people in the control phase

**Potential Impact:** Addressing the syndemic between tobacco use and HIV infection in a coordinated manner aligns with the NIH HIV/AIDS priorities for effective cancer control among PLWH in a high HIV prevalence setting. This study is significant because it integrates smoking cessation interventions, which are lacking in sub-Saharan Africa (SSA), into a real-world HIV care system that has been underpinned by a robust PEPFAR/CDC program and leverages long-standing partnerships with Ministry of Health and Wellness and the University of Botswana's Anti-tobacco Network for population, health system, and policy level impact.

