#### Secondary Outcomes:

- Quit attempts
- Length of successful quitting during each attempt
- Number of cigarettes currently smoked, and
- Number of days of using combustible tobacco products for at least 24 hours within the past month and the last 3 months.

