### Estimating process and outcome measures

All procedures will be conducted according to the local standards of routine clinical care. The following measures will be utilized:

1. **Baseline Demographic Information:** Baseline information will be abstracted from the HIV medical records and collected using a questionnaire. Baseline information will include demographics, medical history, laboratory values measured as part of HIV care (e.g. viral load, CD4), antiretroviral (ARV) history and ART treatment regimen (for current patients), and ART treatment start date. Because of high viral load suppression and high retention rate in this population, we will not be analyzing HIV treatment variables as mediators or outcomes.
2. **5”A”s (SBIRT) checklist:** This checklist will be completed by the LHW case managers and will serve to document the delivery of the intervention. A 10% random sample of the completed 5”A”s checklist will be reviewed by [name] during the time that a site is engaged in the intervention to ensure fidelity to the study intervention.
3. **Intake Smoking History Questionnaire** will measure length of smoking, use of other tobacco products, quit attempts, length of longest quit attempt, and smokers in the immediate living environment.
4. **Follow-up Smoking Use Questionnaire** will measure 7-day and 30-day point prevalence abstinence, number of cigarettes smoked (if not abstinent), stage of change and readiness to quit (if not abstinent), length of longest period of abstinence since last evaluation, use of varenicline, side effects, reasons for using or not using varenicline, and length of varenicline use.

5. **Stages of Change Algorithm** and **the Readiness Ruler**, will be used at baseline and follow-up to determine each individual's stage of change for quitting tobacco.
6. **Smoking Abstinence**: Abstinence will be based on self-reported 7-day point prevalence abstinence confirmed by expired CO < 6 ppm. Abstinence criteria must be met in participant Month 6 or at an earlier study week and maintained through participant Month 6 to be considered a responder. We will use coVita CO Smokerlyzer, a single-breath point-of-care tool designed specifically for use in smoking cessation programs and clinics.

For those who agree to be treated with varenicline:

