## Power and Sample size

Our sample size is based on the hypothesis that interventions will have a substantial impact on primary endpoints compared to the control phase (Figure 5).

**Main effect:** Based on a meta-analysis of 24 randomized controlled trials in LMIC, smoking abstinence at 6 months follow-up ( $P_{\text{control}}$ ) for usual care averages 10% (range, 8% to 14%). Assuming withdrawal from trial follow-up or loss to follow-up to be 5%, our sample of 25 PLWH per cluster per period has power of 87% to detect at least 10% increase (main effect,  $\Delta = (P_{\text{implementation}} - P_{\text{control}})$ ) in the primary endpoint at six months with the assumption that the event rate for those in control phase is 10% and two-sided alpha at intra-cluster correlation of 0.02.

[figure not shown]

Fig 5. Power to detect primary endpoint, main effect versus standard of care (SOC)

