| 5. | 
Since your last study visit, have you ever quit for a period of at least 24 hours?
 
If No, skip to Q9.
                                                                                                                                                                                                                                                                                    |  Yes
 No                                                                                                                                                                                                                                                                                                   |
| 6. | 
Since your last study visit, how many times have you quit for at least 24 hours? (If more than 9 times, put 9)
                                                                                                                                                                                                                                                                                         | 
_____ times
                                                                                                                                                                                                                                                                                                                                            |
| 7. | 
After your most recent quit attempt, how long did you stay off cigarettes?
                                                                                                                                                                                                                                                                                                                             |  1-2 days
 A week
 2-4 weeks
 Over 4 weeks                                                                                                                                                                                                           |

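### Hypothesis iii compares abstinence length only in failed quit attempts, a set BSMART is meant to change, and it conflicts with the listed secondary outcome

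*Protocol*

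**What the plan says.** The Hypothesis section of the protocol lists six directional hypotheses, each comparing people exposed to BSMART with people in the control phase. The first is "Increase the proportion of smokers able to quit smoking", the second "Increase the number of attempts to quit smoking" and the third "Increase the length of abstinence in failed quit attempts".

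Three other places deal with the same quantity, and none restricts it to failures:

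- Secondary Outcomes (Process and Outcome Measures) lists "Length of successful quitting during each attempt".
- Estimating process and outcome measures, item 4, says the follow-up questionnaire will record "length of longest period of abstinence since last evaluation".
- The questionnaire itself (Appendix B4, question 7) asks "After your most recent quit attempt, how long did you stay off cigarettes". There are four answer categories, the highest being anything beyond four weeks.

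The Statistical Analysis section for Objective 1 gives no model for length of abstinence.

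**The concern.** Whether an attempt fails is known only after the participant has been exposed to one phase or the other, and changing it is the purpose of the intervention. Restricting to failed attempts removes from the implementation phase the attempts that BSMART turned into successes. Any additional attempts that BSMART prompts also enter that phase, and the failed ones join the set. The failed attempts in the two phases are then different selections of attempts. Stepped-wedge allocation does not protect a comparison within them, and no covariance structure or small-sample correction restores it.

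At stake is the reading of one secondary result. A null or negative finding within failures could be reported as BSMART not lengthening, or even shortening, abstinence when abstinence over all attempts had become longer. The four places also leave it open whether the outcome is measured in failed attempts, each attempt, the most recent attempt, or as the longest period.

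**Working it through.** **1. Reproduce the plan's figure, to confirm the quit rates.** Power and Sample size assumes 10% abstinence in the control phase and states that "our sample of 25 PLWH per cluster per period has power of 87% to detect at least 10% increase", with 5% loss, an intra-cluster correlation of 0.02 and 15 facilities. The alpha value is not printed; 0.05 two-sided is assumed.

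- Cluster-period size after loss: 25 × 0.95 = 23.75
- Per phase: 15 × 23.75 = 356.25
- Design effect: 1 + (23.75 − 1) × 0.02 = 1.455
- Effective size per phase: 356.25 / 1.455 = 244.8
- Two-proportion power, 10% versus 20%: 0.875, against the stated 87%

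So 10% versus 20% is the planned scenario. The protocol gives no figure for length of abstinence.

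**2. Size of the selection.** Taking one attempt per person, failures fall from 90% to 80% of attempts. The share of would-be failures that leaves the set is (90 − 80) / 90 = 1/9. With 375 per phase, that is 337.5 failures against 300.

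**3. How the two means relate.** Let *p* be the success proportion, *F* the mean length in failed attempts and *M* the mean over all attempts, with success counted as 24 weeks (168 days). Then

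*M* = (1 − *p*) × *F* + 168 × *p*.

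With *p* at 0.10 and 0.20, *M* can rise while *F* stands still or falls.

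**4. Range of results.** Each assumed duration distribution is scaled to give 10% success in control. Four ways of reaching 20% under BSMART are compared: every duration lengthened by a common factor; a random ninth of failures converted; conversion probability rising in proportion to duration rank (graded); and conversion of exactly the longest-lasting failures. Means are in days, control to BSMART.

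| Distribution | Mechanism | Failed only | All attempts |
|---|---|---|---|
| Exponential | Common factor | 54.3 to 62.4 | 65.7 to 83.5 |
| | Random | 54.3 to 54.3 | 65.7 to 77.0 |
| | Graded | 54.3 to 51.3 | 65.7 to 74.6 |
| | Longest converted | 54.3 to 43.6 | 65.7 to 68.5 |
| Weibull, shape 0.5 | Common factor | 28.5 to 35.5 | 42.5 to 62.0 |
| | Random | 28.5 to 28.5 | 42.5 to 56.4 |
| | Graded | 28.5 to 26.2 | 42.5 to 54.6 |
| | Longest converted | 28.5 to 17.4 | 42.5 to 47.5 |
| Lognormal, sigma 2 | Common factor | 25.1 to 35.6 | 39.4 to 62.1 |
| | Random | 25.1 to 25.1 | 39.4 to 53.7 |
| | Graded | 25.1 to 23.1 | 39.4 to 52.1 |
| | Longest converted | 25.1 to 14.8 | 39.4 to 45.4 |

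Hand check, exponential control: scale = 168 / ln 10 = 72.96; *M* = 72.96 × 0.9 = 65.7; *F* = (65.7 − 16.8) / 0.9 = 54.3. For longest converted: *M* = 0.8 × 43.6 + 0.2 × 168 = 68.5.

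The failed-only difference runs from 17.4 − 28.5 = −11.1 days to 35.6 − 25.1 = +10.5 days. The all-attempt difference is positive in every row, from 68.5 − 65.7 = 2.8 to 62.1 − 39.4 = 22.7 days.

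**5. How often a test would mislead.** Simulated trials used 375 per phase, one attempt each, Weibull durations, a rank test and no clustering. The failed-only result was significantly shorter under BSMART in about 13% of trials with graded conversion and about 67% when exactly the longest failures were converted. Random conversion gave 5%, the nominal level. Under a hazard lowered equally for everyone, the failed-only test had about 60% power and the all-participant test about 98%.

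**The case against.** The strongest reply is that the protocol fixes no failed-only test. The hypothesis is one line, no model is named, and detail on a secondary outcome may properly sit in a statistical analysis plan that is not shown. This stands as far as the method goes: a missing model is not the complaint. It does not dispose of the point, because the protocol does state the comparison set, and states it differently from its own outcome list and measures.

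A reader might draw several stronger conclusions that the documents do not support:

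- **A reversal is to be expected.** The 67% figure needs BSMART to rescue exactly those who already hold out longest. Nothing in the protocol says it does.
- **The more effective BSMART is, the more the failed set loses its long attempts.** This is not a rule. Random conversion leaves the failed-only mean unchanged, and uniform lengthening raises it.
- **The 5% under random conversion is lost power.** No failed attempt is lengthened there, so hypothesis iii is false by construction and 5% is the correct error rate.
- **BSMART adds weaker attempts.** The second hypothesis speaks only of the number of attempts, not of their strength.

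The simulation is also simplified. The questionnaire allows up to nine attempts per interval, so an eventual quitter can contribute failed attempts too. Clustering is ignored, so the rejection rates are higher than a correctly clustered test would give.

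**Conclusion.** The concern holds as a badly stated comparison and an internal contradiction. Hypothesis iii conditions on an outcome that hypotheses i and ii say BSMART changes, and its sign is not determined by whether BSMART lengthens abstinence. At 10% versus 20% success it can show a gain, no difference or a loss: about −11 to +10 days within failures, against +3 to +23 days over all attempts. A significant false reversal is possible rather than likely: about 13% of unclustered trials under graded conversion, and about 67% only in the extreme case.

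These sizes rest on assumed duration distributions and conversion mechanisms, one attempt per person, and 168 days credited to each success. The selection argument and the textual conflict do not depend on those assumptions. This is one secondary hypothesis with no stated power; the primary endpoint and its 87% are not affected.

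**What to change.** Reconcile the Hypothesis section, Secondary Outcomes, item 4 of Estimating process and outcome measures, and Appendix B4 question 7. State both the hypothesis and the secondary outcome as the longest period of abstinence over 24 weeks in all enrolled participants, with 0 if no attempt was made and the value capped at follow-up length if still abstinent. Compare phases on means, with a model that accounts for clustering by facility. Report length within failed attempts descriptively only.

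The cost is small but goes beyond wording:

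- **Questionnaire.** Question 7 asks about the most recent attempt and does not distinguish lengths beyond four weeks. It must record the longest abstinence, with enough resolution above four weeks. Because visits fall at weeks 4, 12 and 24, a period that spans a visit also has to be joined across forms. In the unclustered simulation, recoding durations to the present categories cut all-participant power to 39% under random conversion, against 68% with continuous durations, and to 14% under graded conversion.
- **Overlap.** The restated outcome shares more information with the primary endpoint.
- **Power.** The change removes the selection but does not guarantee detection. When exactly the longest failures are converted, an all-participant rank test rejects in only about 6% to 8% of trials, which is one reason to compare means.
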